## Design

### Trial design

The effectiveness of an educational intervention combining practice-based workshops and computer based support will be tested in a pragmatic unblinded cluster randomised controlled trial with a pre-post design and with two arms; normal care versus educational intervention (see consort diagram in Figure 1). The researchers will be aware of group allocation but carers and people with dementia will not be informed.

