### Sample size

Based on the study having 90% power to detect as significant, using a 5% 2-tailed significance level, a difference in the proportion of individuals with 2 or more dementia related GP visits of 50% (control: 20% versus Intervention: 70%) the required sample size, based on individual randomisation would be 23 per group - a total of 46 individuals. However, due to the use of cluster randomisation, the total required sample size needs to be inflated in order to take account of this clustering. The number of patients recruited per practice will also need to be inflated in order to maintain the sample sizes in the presence of attrition [19,20]. With 20 practices (10 per arm), the power to detect the differences postulated would be maintained if the ICC were of the order 0.37 or less. Thus the effective sample size with 10 patients per cluster and 20 practices would need to be 200. If the expected attrition rate were 1/3 (33.3%) then 15 patients would need to be recruited per practice in order to maintain the sample size of 10 patients per practice.

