### Procedure

All practices will be asked to identify patients with symptoms of dementia by using electronic searches of their clinical record system updated by manual checks of the resulting list by medical and nursing staff. Where there is no informal carer eligible for interview, advice regarding consent for examination of medical records will be sought from an appropriate consultee. No personalised information will be retained following the record examinations, which will be carried out in the surgery by research team members who have honorary contracts with the relevant PCT.

This trial will last 36 months allowing for a follow-up period of 12 months that will capture effects on clinical practice, carer satisfaction, met and unmet needs. Data will be gathered before and 12 months after the introduction of the educational interventions.

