### Statistical analyses

We will assess the effect of the interventions at the practice level because the data will be cluster based and analyses will be performed on an intention to treat basis. Analyses of all quantitative responses will be performed with a general linear model with the arm and time as fixed effects and practice identity as a random effect.

We will analyse differences in detection rates by using binary logistic regression to include the cluster effect. These will be calculated before and after the intervention, excluding cases previously diagnosed in another practice. Concordance scores for diagnosis and management before and after the intervention will not directly be comparable as they comprise counts of actions taken over two different lengths of time. We will use Vickers' method and examine differences in baseline concordance scores across the arms of the study and then repeat the analysis for scores after the intervention. This analysis will also incorporate the cluster effect.

If outcome data are missing, we will assume they are "missing at random" (MAR). This means that the probability of missing data can be predicted by variables measured at baseline. In this case, an analysis which adjusts for the baseline predictors of 'missingness' (at least baseline response and treatment) will give an unbiased estimated of the treatment effect, making multiple imputation unnecessary. Multiple imputation will be used only if important baseline predictors are missing. Methods will then be employed which take account of the clustered nature of the data

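### For quantitative secondary outcomes measured twice on the same patients, a model with practice as its only random effect gives the wrong standard error for any intervention effect on change

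*Protocol article*

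**What the plan says.** The Trial design section describes a "pragmatic unblinded cluster randomised controlled trial with a pre-post design and with two arms", and the Procedure section adds: "Data will be gathered before and 12 months after the introduction of the educational interventions". The Statistical analyses section opens with "We will assess the effect of the interventions at the practice level because the data will be cluster based" and then gives one model for all quantitative responses: a "general linear model with the arm and time as fixed effects and practice identity as a random effect". It names no patient effect, no practice-by-time effect and no arm-by-time term.

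The article does not say outright that the same patients are scored twice, but three features point that way: consent is individual (Consent), recruitment rises from 10 to 15 per practice to cover attrition of one third (Sample size), and the missing-data paragraph refers to adjustment for baseline response (Statistical analyses).

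Other outcomes have their own analyses. Detection rates go to logistic regression with a cluster effect. Concordance scores are compared between arms at baseline and again after the intervention. The primary outcome is binary. The general linear model therefore serves the remaining scores: unmet needs (Secondary outcome), and the quality of life and carer strain named in the Abstract.

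**The concern.** Two sources of variation matter when change is compared between arms of a cluster-randomised cohort. The first is the patient: two scores from one person are usually correlated beyond what a shared practice explains, and a difference within the person removes that part. The second is practice drift: practices may change by different amounts over 12 months for reasons other than arm. The Discussion section itself expects local programmes under the National Dementia Strategy to influence practices.

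A single practice intercept represents neither. A change effect is then judged against pooled within-practice residuals instead of against variation in change among 20 practices. Ignoring the patient term makes the standard error too large; ignoring drift makes it too small. Adding an arm-by-time term supplies the estimate of change but leaves the error term as it was. At stake is whether the patient and carer score results come out falsely null or falsely positive, with nothing in the fitted model to show which.

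**Working it through.** **The plan's own figures.** With 20% versus 70%, two-sided 5% and 90% power, the uncorrected formula gives [1.96√(2×0.45×0.55) + 1.2816√(0.16+0.21)]²/0.5² = 18.6, so 19 per group. With continuity correction it is 22.5, so 23, matching "based on individual randomisation would be 23 per group - a total of 46 individuals". With 100 patients per arm the tolerable design effect is 100/23 = 4.35, so the largest ICC is (4.35 − 1)/9 = 0.372, matching "the power to detect the differences postulated would be maintained if the ICC were of the order 0.37 or less". For attrition, 10/(1 − 1/3) = 15. All reproduce.

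**Inputs for the check.** From the Sample size section: k = 10 practices per arm, m = 10 patients per practice, and ICC 0.37 as the upper limit. From Procedure: two time points. Assumed, because the article gives neither: CAC, the correlation of a practice's effect over time, 0.5 to 1; and r, the within-patient correlation given practice, 0 to 0.8. Total variance is 1.

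**Formulas for the arm difference in change.**
- Practice-by-time variance: a = ICC(1 − CAC). Patient variance: b = (1 − ICC)r. Residual variance: e = (1 − ICC)(1 − r).
- True variance: 4(a/k + e/(km)).
- Variance reported by the practice-only model with arm-by-time added: 4·MSW/(km), with MSW = [18(ma + e) + 180(2b + e) + 180e]/378. The degrees of freedom are 400 − 20 − 2 = 378. A practice-level test of change has 20 − 2 = 18.

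**ICC 0.37, CAC 0.8, r 0.5.** a = 0.074, b = e = 0.315. True variance = 4(0.0074 + 0.00315) = 0.0422, SE 0.205. MSW = (18×1.055 + 180×0.945 + 180×0.315)/378 = 0.650; reported variance 0.0260, SE 0.161. The ratio is 0.79, so true size is 2[1 − Φ(1.96×0.785)] = 12.4%.

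**ICC 0.05, CAC 1, r 0.5.** a = 0, b = e = 0.475. True variance = 0.019, SE 0.138. MSW = (18×0.475 + 180×1.425 + 180×0.475)/378 = 0.927; SE 0.193. The ratio is 1.40 and size 0.6%.

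| ICC | CAC | r | Reported SE / true SE | Size |
|---|---|---|---|---|
| 0.37 | 0.9 | 0.5 | 0.96 | 6.0% |
| 0.37 | 0.8 | 0.5 | 0.79 | 12.4% |
| 0.37 | 0.7 | 0.5 | 0.68 | 18% |
| 0.37 | 0.5 | 0.5 | 0.57 | 26.4% |
| 0.20 | 0.8 | 0.5 | 1.00 | 5.0% |
| 0.10 | 0.8 | 0.5 | 1.17 | 2.2% |
| 0.05 | 0.9 | 0.5 | 1.33 | 0.9% |
| 0.05 | 1 | 0.5 | 1.40 | 0.6% |

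Over the whole assumed range the ratio runs from 0.54 to 2.19. Simulation agrees, giving about 6%, 13%, 17% and 26% for the first four rows. A t-test on practice mean changes (18 df) stays close to 5% throughout.

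**Power for a 0.3 SD effect at ICC 0.05, practice-only model versus practice-level test of change.** About 28% v 54% (CAC 1, r 0.5), 30% v 50% (CAC 0.9, r 0.5) and 26% v 69% (CAC 0.9, r 0.7).

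**The literal arm effect.** Its simulated size is 4.5% to 5.5%, which is sound. But it averages the two time points, so an effect δ present only at follow-up is estimated as δ/2. At ICC 0.05, CAC 1, r 0.5, the variance of a practice's two-time mean is 0.05 + (0.475 + 0.475/2)/10 = 0.121. The SE of the arm difference is √(2×0.121/10) = 0.156, and 0.15/0.156 = 0.96 gives power of about 15% for δ = 0.3 SD.

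**The case against.** The strongest reply is that the criticised test is not in the article. The model has no arm-by-time term, and its arm effect has correct size. That stands: a reader might infer that the stated test has an inflated false-positive rate, and it does not. The cost of the literal reading is dilution instead.

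Second, the sentence about assessing effects at practice level may mean that the model is fitted to practice means. Practice is then the only random effect needed, and once arm-by-time is included the error-term problem disappears. This also stands as a possible reading. The ICC-based sample size and the adjustment for baseline response favour patient-level rows, but the text does not settle it.

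Third, a condensed article may leave random-effects detail to an analysis plan. This carries less weight, because the article does not defer the random part; it states one.

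Fourth, the inflated rates in the table use ICC 0.37, which the article gives only as the largest value at which power for the binary outcome holds. It is not an expected value for questionnaire scores. With r 0.5 and CAC 0.8, the test is already conservative at ICC 0.10. This stands, and it is why the direction of error must be left open.

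Fifth, the missing-data paragraph already describes an analysis adjusting for baseline response and treatment. That is close to the remedy, but it is offered only for missing outcomes and not as the main analysis.

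**Conclusion.** The point holds for quantitative secondary scores measured on the same patients at both times, if the model is fitted to patient-level rows. As written, it yields either a diluted arm effect of correct size or, once a change term is added, an effect with a wrong standard error. That error is too large where within-patient correlation dominates (size about 1% or less at ICC 0.05 with CAC 0.9 to 1 and r 0.5; power about 28% against 54% with no drift). It is too small where practices drift apart (size about 6% to 26% at ICC 0.37, CAC 0.9 to 0.5, r 0.5). CAC and r are assumptions throughout, and the two errors can offset each other.

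A reader might go further and infer that the primary result or the concordance findings are at risk. The article does not support that: the primary outcome is binary, and concordance scores are compared separately at each time. Nor does the model treat a patient's two scores as fully independent. They are independent given practice, and so correlated at the level of the practice ICC. The matter deserves correction because the remedy is simple, but it does not bear on the trial's main conclusion.

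**What to change.** For quantitative outcomes measured at both times, replace the pooled model with one that has the 12-month score as outcome, arm and the patient's baseline score as fixed effects, and practice as random effect. Use small-sample degrees of freedom suited to 20 practices (for example Kenward-Roger). Each patient then contributes one outcome row, and the arm coefficient is the intervention effect at follow-up.

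An alternative with the same aim keeps both time points, adds arm-by-time, and adds patient and practice-by-time random effects, again with small-sample degrees of freedom. If practice means are intended, say so and include arm-by-time.

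The cost is a few lines in the Statistical analyses section; no further patients or measurements are needed. Intervals may be wider where practices do drift differently, and with 20 practices some variance components may be estimated near zero, so the plan should say what is done in that case.

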#### Secondary outcome

1) Concordance with guidelines.

We will transcribe and scrutinise manual and electronic records for the recording of actions considered to be best practice in the diagnosis and management of dementia in primary care by using the NICE/SCIE dementia guidelines [2]. Appendix 1 shows the components of good practice that will be captured. The index consultation is the one where the suspicion of possible dementia is first recorded (Appendix 2).

2) Measurement of unmet needs in patients and carers.

Unmet needs will be captured using a questionnaire developed and validated by us in a previous trial [18].

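### Follow-up concordance scores are compared between arms with no stated adjustment for baseline, which costs precision and leaves the result exposed to chance imbalance among 20 practices

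*Protocol article*

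**What the plan says.** Guideline concordance is the first of the two numbered items under Secondary outcome ("1) Concordance with guidelines"). Its components, six for diagnosis and seven for management, are listed in Appendix 2. The section Statistical analyses states that scores from before and after the intervention "will not directly be comparable as they comprise counts of actions taken over two different lengths of time". It continues: "We will use Vickers' method", and the plan is to "examine differences in baseline concordance scores across the arms of the study and then repeat the analysis for scores after the intervention". It adds: "This analysis will also incorporate the cluster effect". The named method is neither defined nor referenced.

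Two other statements in the same section bear on this outcome. All quantitative responses are to be analysed with a "general linear model with the arm and time as fixed effects and practice identity as a random effect". If outcome data are missing, the section relies on an analysis that "adjusts for the baseline predictors of 'missingness' (at least baseline response and treatment").

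Under Procedure, data are gathered before the intervention and 12 months after it. Under Sample size, 20 practices are planned, 10 per arm, with 10 patients each after an attrition of one third.

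**The concern.** Repeating the baseline analysis on the later scores means, on its ordinary reading, the same between-arm comparison with the same terms. This raises three problems.

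- Practices are randomised, so any baseline difference between arms is due to chance. A baseline comparison made as a test addresses a null that allocation makes true, and its result does not show whether the imbalance matters for the outcome.
- Two comparisons side by side do not give an estimate of the intervention effect net of baseline.
- The observation about unequal time spans is sound, but it supports a narrower conclusion than the one drawn. Subtracting one count from another needs a common exposure time. Regressing one on the other does not, because the slope absorbs the difference in scale.

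At stake is the precision of an outcome close to the trial's stated challenge of changing clinical management, and how far its result depends on the imbalance that a draw of 20 practices happens to produce.

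**Working it through.** **The plan's own figures.** No SD, ICC, effect size or correlation is given for concordance. The design figures for the primary outcome do reproduce. For 20% v 70%, 90% power and two-sided 5%, the continuity-corrected size is 23 per group. With 100 patients per arm in practices of 10, 100/(1 + 9 × ICC) = 23 gives ICC = 0.372, against the stated 0.37. With one-third attrition, 10/(1 − 1/3) = 15 per practice.

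**Inputs.** From Sample size: 10 practices per arm, 10 patients per practice. Assumed, because the article gives neither for concordance: ICC 0.05 to 0.37 (the upper end borrows the primary-outcome tolerance) and correlation r of baseline and follow-up practice means 0.3 to 0.7.

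**Step 1: chance imbalance at baseline.** In units of the patient SD, the SD of the between-arm difference is √(2 × [ICC + (1 − ICC)/10]/10).

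- ICC 0.05: √(2 × 0.145/10) = 0.170, so 95% limits ±0.33.
- ICC 0.37: √(2 × 0.433/10) = 0.294, so 95% limits ±0.58.

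A share r of the observed imbalance carries into an unadjusted follow-up difference. For a 1-SD imbalance this runs from 0.3 × 0.170 = 0.05 to 0.7 × 0.294 = 0.21 patient SD.

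**Step 2: precision.** Adjustment multiplies the variance of the arm effect by 1 − r². Estimating the slope from 20 practices in two arms costs a factor of about 1 + 1/(20 − 4) = 1.0625.

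| r | 1 − r² | × 1.0625 | Net cut in variance | Unadjusted 80% power becomes |
|---|---|---|---|---|
| 0.3 | 0.91 | 0.967 | about 3% | about 81% |
| 0.5 | 0.75 | 0.797 | about 20% | about 88% |
| 0.7 | 0.51 | 0.542 | about 46% | about 97% |

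The power column compares a t test on 18 df with an analysis of covariance on 17 df.

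**Step 3: error rate.** Under a true null, with a baseline imbalance of b standard errors, the unadjusted follow-up statistic is approximately normal with mean r × b and variance 1 − r². Its chance of exceeding ±1.96 is:

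| | r = 0.5 | r = 0.7 |
|---|---|---|
| b = 0.5 | 3.0% | 1.3% |
| b = 1.5 | 8.2% | 10.1% |
| b = 1.9 | 12.2% | 18.9% |
| All non-significant baselines (b within ±1.96) | 4.3% | 3.5% |
| All randomisations | 5.0% | 5.0% |

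An absolute imbalance between 1.5 and 1.9 SE occurs in 2 × [Φ(1.9) − Φ(1.5)] = 7.6% of randomisations. A simulation of 20 practice means (200,000 runs, t thresholds) gave 4.9% to 5.0% overall for the unadjusted test. At an imbalance of 2 SE it gave 7.9%, 12.3% and 19.6% for r = 0.3, 0.5 and 0.7. The adjusted analysis stayed at about 5% in every case.

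**The case against.** **The absence of adjustment is inferred.** The article does not call the analysis unadjusted, and the named method might involve baseline in some way. That cannot be settled from an article that does not define it. This stands as a limit on certainty. But the sentence goes on to describe the procedure, and what it describes has no baseline covariate.

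**Baseline adjustment appears elsewhere in the section.** The missing-data clause adjusts for baseline response, and with one-third attrition allowed for, it may well apply. The arm-and-time model may also use baseline as a repeated response. So a reader who infers that the baseline score is wasted goes too far. Neither statement, however, supplies a baseline-adjusted model for concordance. Together with the two-step text they leave more than one candidate analysis for the same outcome.

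**The false-positive rate is not inflated overall.** A reader might infer that a non-significant baseline comparison followed by a significant follow-up one is usually carried-over imbalance, with error of 8% to 19%. Those rates hold only for the 7.6% of randomisations with an imbalance of 1.5 to 1.9 SE, at r of 0.5 to 0.7. Over all non-significant baselines the rate is below 5%. The follow-up estimate is also unbiased over randomisations.

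**The gain may be small.** At r = 0.3 it is about 3% of the variance. This stands.

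**A patient-level baseline may not exist.** Diagnosis items run from the index consultation, so patients first suspected during follow-up may have no earlier score. This stands, and it affects the choice of covariate.

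**Conclusion.** The point holds as one of efficiency and of error conditional on the observed imbalance, for a secondary outcome. As written, concordance is compared between arms twice, with no baseline covariate named, and the reason given does not justify leaving one out. The likely cost is between about 3% and 46% of the variance of the arm effect, for assumed practice-mean correlations of 0.3 to 0.7. The article contains no figure that would narrow this range. The calculations also assume approximately normal practice means and equal arms of 10. The documents do not support a claim of systematic bias or of an overall false-positive rate above 5%, and the primary outcome is not affected by this sentence.

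**What to change.** Make the main analysis of each concordance score a single model: follow-up score on arm, adjusted for baseline concordance, with a random practice effect and small-sample degrees of freedom. Report the adjusted difference with a 95% CI. Use the patient's own baseline score for management concordance where it exists. Use the practice's baseline mean where it does not, for example for diagnosis concordance in newly suspected cases. Present baseline scores by arm descriptively, without a test.

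In the same edit, define the named method, and say how this model relates to the arm-and-time general linear model and to the missing-data clause, so that one analysis of concordance is fixed before the data are seen.

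Baseline and follow-up data are already to be gathered, so the cost is mainly wording, plus the work of forming practice baseline means where those are used. Statistically it costs one degree of freedom at practice level (17 rather than 18), with little return if the correlation proves low.

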### Trial management

The trial will be led by the Principal Investigator, [name] and managed by the Programme Manager [name]. The trial co-ordinating centre is the Department of Primary Care and Population Health at University College London. A Trial Management Committee will meet every two months to review the progress of the trial and its members will be recruited from; 1) the research teams in the EVIDEM programme and; 2) patient and public representatives working with the EVIDEM programme. A Trial Steering Committee (TSC) with a majority of members independent of the EVIDEM programme will meet six monthly to review the study. Because there were no adverse outcomes in the earlier trial of educational interventions, we propose not to have a data management committee but to give the chair of the TSC powers to convene a data management sub-group should there be any need to consider adverse events.

### Stopping rules and discontinuation

Participants can chose to leave the trial at any point. The trial will be terminated if it is shown to have a negative impact on routine medical care.

### Duration of the trial

The Trial will run for 36 months depending on the speed of recruitment of practices. Practices randomly allocated to receive training will receive this within three months period, with data collection at baseline and again at 12 months following baseline assessment.

### Participant involvement

Practices will receive regular updates on the trial's progress via newsletters and other media and will also be invited to annual summer schools and seminars run by the EVIDEM programme. This will include receiving study findings at the end of the Trial. Practices allocated to the control arm will receive training after the data collection period. The people with dementia and carers who participate will be offered an option to receive a lay version of the study outcomes and be invited to a lay conference at the end of the study period.

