#### Workshops

The EVIDEM programme has developed a workplace-based approach to training GPs in dementia diagnosis and management. The essential components of this approach are an 'educational needs assessment' and an 'educational prescription'. The educational needs assessment requires a one hour group meeting in the workplace, with the membership of the group determined by the work unit - in our case, the general practice. The facilitator of the group uses a standard checklist to elicit the strengths and weaknesses of the organisation's current practice with people with dementia (see Figure 2). Because inexperienced professionals often misjudge their learning needs, silences and absences in this discussion are interpreted by the facilitator. For example, it is possible for a general practice to discuss dementia care for most of the hour without mentioning carers' needs; the facilitator must point this out. The group can then identify the highest priority topics for learning and decide how it wishes those topics to be presented - as workshops, in an electronic format for self-directed learning, or with a printed manual (Appendix 1).

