#### Intervention

Participating practices will be randomised by an independent person to intervention or control arms using a computer generated randomisation programme. Practices randomly allocated to the intervention arm will be asked to participate in tailored learning activities consisting of an educational needs assessment followed by up to three face-to-face educational workshop sessions on dementia over a three-month period and will be given electronic resources which they can use during and after consultations with people with known or suspected dementia syndrome. Each educational workshop will be arranged at dates/times convenient to the practice team.

An experienced general practitioner with a background in postgraduateeducation will facilitate the small group workshops with the practice team. Tailoring of the education programme is carried out in a three step process: 1) in the first workshop, an educational needs analysis is undertaken using a standard checklist to identify aspects of dementia care which the practice perceives as problematic for them; 2) a prescription to meet the practice team's educational needs is then written to address shortcomings and sorting out the appropriate written educational resources, and; 3) the best forms of learning are then identified with a delivery and discussion with the team of the selected educational resource materials in the light of their perceived needs.

The 'normal care' arm will be given a summary of the NICE/SCIE dementia guidelines [2] and offered workshop training and electronic tools and resources at the end of the study. General practitioners, practice nurses and any other staff involved will be invited to give feedback on the educational resources.

Practices will be offered financial reimbursement to cover the use of locums and data collection costs (e.g. recruitment of patients and carers). Payments will be based on a sliding scale according to the number of partners in the practice, up to a maximum allocation.

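### Control practices are not excluded from the programme's annual summer schools and seminars before their 12-month outcomes are extracted, which may dilute the contrast between arms

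*Protocol article*

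**What the plan says.** Under Participant involvement, the article states that practices get regular updates on the trial's progress and "will also be invited to annual summer schools and seminars run by the EVIDEM programme". That sentence is not restricted to one arm or to a period. Later in the same paragraph the control arm is named separately, but only for its training: "Practices allocated to the control arm will receive training after the data collection period". The Intervention section agrees with this. The normal-care arm gets a guideline summary and is "offered workshop training and electronic tools and resources at the end of the study".

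The programme that runs the events is also the one behind the intervention. The Workshops section says: "The EVIDEM programme has developed a workplace-based approach to training GPs in dementia diagnosis and management".

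On timing, the Procedure section says: "This trial will last 36 months allowing for a follow-up period of 12 months that will capture effects on clinical practice". Duration of the trial describes training within three months, "with data collection at baseline and again at 12 months following baseline assessment". Nothing in the article delays the event invitation for control practices or provides for recording who attends.

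The Discussion lists, as a limitation, that local education linked to the National Dementia Strategy may influence practices. It does not mention the programme's own events.

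**The concern.** The trial compares education with normal care. The plan protects that contrast by withholding one educational route from controls (training, workshops, electronic tools) until outcomes are in. Read as written, it leaves a second route open, run by the same programme.

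Both affected outcomes record what clinicians do. The primary outcome is the proportion of patients with at least two dementia-specific reviews in a year, and the concordance scores count recorded actions. If control clinicians learned something at an event that changed their practice, the control rate would rise and the observed difference would shrink. An intention-to-treat analysis would not undo that. Without attendance records, the trial could not describe how much exposure had occurred.

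**Working it through.** **1. Who and when.**
- The invitation goes to practices in general. The one sentence that singles out controls defers training only. Controls are therefore within the invitation as written.
- Events are annual. Outcomes are taken 12 months on, within a 36-month trial. An event held once a year would fall about once in each practice's 12-month window. This follows from the word annual; the article gives no dates.

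**2. Reproducing the plan's own figures.** Inputs from Sample size: "Based on the study having 90% power to detect as significant, using a 5% 2-tailed significance level"; rates "control: 20% versus Intervention: 70" per cent; 20 practices, 10 per arm; 10 analysed patients per practice; ICC up to 0.37.
- Two-proportion formula without correction, mean proportion 0.45: n = [1.96·√(2·0.45·0.55) + 1.2816·√(0.2·0.8 + 0.7·0.3)]² / 0.5² = 18.6, so 19 per arm.
- With continuity correction: n' = (18.64/4)·[1 + √(1 + 4/(18.64·0.5))]² = 22.5, so 23 per arm. This matches the plan's 23 per group (46 in total).
- Design effect = 1 + (10 − 1)·ICC. Largest tolerable ICC = (200/46 − 1)/9 = 0.372, which matches 0.37.
- At ICC 0.37 the design effect is 4.33, so effective n per arm = 100/4.33 = 23.1.

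The plan's arithmetic is sound and is not in dispute.

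**3. Power if the control rate rises.** The rises are assumptions; the article gives none. The intervention rate is held at 70%.

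Power = Φ{ [d − 1/n − 1.96·√(2·p̄(1 − p̄)/n)] / √[(p₁(1 − p₁) + p₂(1 − p₂))/n] }, where d = p₂ − p₁, p̄ is the mean of the two rates and n is effective n per arm.

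Worked case, control 30%, ICC 0.37: d = 0.40, 1/n = 0.0433, p̄ = 0.50. The numerator is 0.3567 − 0.2884 = 0.0683, the denominator is 0.1349, the ratio is 0.507, and power is 69%.

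| ICC | Effective n per arm | Control 20% | 25% | 30% | 35% |
|---|---|---|---|---|---|
| 0.37 (plan's limit) | 23.1 | 91% | 82% | 69% | 55% |
| 0.20 (assumed) | 35.7 | 99% | 96% | 90% | 79% |
| 0.10 (assumed) | 52.6 | >99.9% | 99.7% | 98% | 94% |

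**4. If both arms rise equally.** At ICC 0.37, with 25% v 75%, 30% v 80% and 35% v 85%, the same formula gives 91%, 91% and 92%. Power is essentially unchanged, because the 50-point difference is preserved.

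**5. What the assumed rises mean.** The planned effect is 50 points. A 5-point rise across the control arm is 5/50 = 10% of it, as if one of ten control practices gained the full effect. A 15-point rise is 15/50 = 30%, as if three of ten did.

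**The case against.** The case against is substantial, and much of it stands.

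- **Content is not stated.** The invitation sits beside progress updates and is followed by a promise of study findings at the end of the trial. It can be read as engagement and dissemination. A reader might infer that these are dementia teaching events delivering the same material as the intervention. The article does not say so. That the subject is dementia is inferred from the programme's own field. The tested intervention (a practice-specific needs assessment, an educational prescription, up to three in-practice workshops and electronic tools) is nowhere linked to the summer schools.
- **An invitation is not attendance.** A reader might take the expectation of innovative early adopters as showing that controls will attend. No attendance figure is given.
- **Any effect could be small.** The Background reports that workshops and decision support in the earlier trial improved detection but did not change management. Occasional seminars might do less.
- **The low power figures are a worst case.** They need the limiting ICC and an intervention arm that gains nothing, although intervention practices are invited too. Steps 3 and 4 show how far the loss shrinks otherwise.
- **The article is condensed.** The full protocol could hold arm-specific rules for these events.

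These points limit the strength of the claim but do not remove it. The article makes a positive statement about who is invited, and it draws an arm distinction for training in the same paragraph without drawing one for the events. A gain in the intervention arm might preserve the difference, but it would not restore a normal-care comparator.

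**Conclusion.** The point holds as a risk that the plan creates and can easily remove. As written, control practices may be exposed to education from the trial's own programme before their outcomes are extracted. The expected direction of bias is towards no effect, for both the primary and the concordance comparisons.

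The size is unknown. Under the assumed control rises of 5 to 15 points with intervention fixed at 70%, power ranges from 82% down to 55% at ICC 0.37, but stays between 99.7% and 94% at an assumed ICC of 0.10. It hardly moves if both arms rise together.

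A reader might go further and conclude that the control arm will be contaminated, or that a null result would be uninterpretable. The article does not support either: content, dates and uptake are unstated, and recording attendance would itself help to interpret a null result.

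**What to change.** State that control practices will be invited to the programme's summer schools and seminars only after their 12-month record extraction is complete, alongside the deferred training. Record any attendance at these events by practice, in both arms, so that exposure can be described when the results are reported. The newsletters need no change on this ground, since the article describes them as updates on the trial's progress.

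The cost is a small loss of goodwill among control practices, which already wait for their training, and a simple attendance log.
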